## Dose Modifications for Toxicity

Dose adjustments are to be made according to the system showing the greatest degree of toxicity (see Table 2).

The most common adverse effects of erlotinib are diarrhoea and skin rash. Other reported adverse effects include fatigue, dry skin, pruritus, anorexia, nausea, vomiting, dry mouth; dry eyes and headache.

In the event of toxicity (e.g., diarrhea, rash) that is not controlled by optimal supportive care, or not tolerated due to any reason, regardless of severity, the daily dose of erlotinib will be decreased to 100 mg/day. A second reduction to 50 mg is possible. Patients who cannot tolerate this dose reduction will be permanently discontinued from the program.

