# Protocol synopsis

| **Title**  PROSPECTIVE EVALUATION OF SMALL MOLECULE EGFR-1 TYROSINE KINASE INHIBITION AS A FIRST-LINE TREATMENT IN PATIENTS WITH ADVANCED NON-SMALL CELL LUNG CANCER (NSCLC) HARBOURING A MUTANT EGFR GENE |
| --- |
| **Sponsor / Study Coordination**  Dienst Medische Oncologie - Oncologisch Centrum  Academisch Ziekenhuis Vrije Universiteit Brussel |
| **Study hypothesis**  Erlotinib is a safe and effective first-line treatment for NSCLC harboring a mutant EGFR |
| **Study design**  One arm, multicenter investigator initiated phase II study. |
| **Primary objective**  To investigate the efficacy and feasibility of using a small molecule EGFR inhibition in the first-line treatment of non-small cell lung cancer carrying (a) EGFR kinase domain mutation(s) not amenable to curative treatment. |
| **Primary endpoint**  Progression free survival time. |
| **Secondary objectives**  Objective response rate according to the RECIST criteria, metabolic response rate Feasibility, toxicity, duration of response and survival (TTP and OS from the date of study entry). |
| **Secondary endpoints**   - Toxicity according to the NCI-CTCAEv3 criteria. - Feasibility (reported descriptively). - Duration of response - Overall survival (from the initiation till PD). |
| **Patient selection criteria**   - - **Identification of an EGFR TKD mutation in the tumor material of the patient.** - No previous chemotherapy for metastatic disease. - Patients in whom any other anticancer treatment is needed after inclusion in the study will be considered to have met the primary endpoint. - Standard phase II recruitment criteria. |

| **Treatment plan and special procedures**  Patients will remain in the study under continuous treatment with erlotinib as long as they remain progression free, receive no other secondary anticancer treatment and remain free from unacceptable toxicity. |
| --- |
| **Study treatment duration, discontinuation and study withdrawal**   - At any time during study, progression of disease, unacceptable toxicity or patient refusal will result in study treatment discontinuation. - Patients that stop study treatment for other reasons than progressive disease must be followed by serial assessment of their response status as provided by the protocol |

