## Dosing Regimen

**The first dose of erlotinib must be given within 1 week after establishment of a gene mutation.**

The mutation status will be communicated via the central data management to the participating investigators. All enrolled patients will receive erlotinib (150 mg/day). No dose escalation of erlotinib is permitted. Erlotinib will be dose reduced for toxicities as detailed in section 12. Toxicity will be graded according to the NCI CTCAE v3.0. Treatment may be delayed for ≤ 2 weeks to allow recovery from toxicity.

Patients will be treated until progression of disease or unacceptable toxicity.

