**Table 2: erlotinib Dose Level Reductions**

| **Starting Dose** | **First Reduction** | **Second Reduction** |
| --- | --- | --- |
| 150mg | 100mg | 50mg |

Within 2 weeks following a dose reduction, erlotinib related toxicity must improve by at least one NCI-CTC grade and be NCI-CTC Grade  2 (Any ocular toxicity must improve to NCI-CTC Grade 1), or further dose reduction by one level will be required. Dosing may be interrupted for a maximum of 2 weeks if clinically indicated and if the toxicity is not controlled by optimal supportive medication.

Once a patient has had a dose reduction for toxicity, the dose will not be re-escalated except in the case of erlotinib related rash. In the event of a rash, dose can be re-escalated when rash is  Grade 2 (see table 3).

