**Table 3: Dosage Modification Criteria and Guidelines for Management of Study Drug Related Toxicities**

| **Toxicity,  NCI-CTC Grade** | **Study Drug Dosage Modification** | **Guideline for Management** |
| --- | --- | --- |
| ***Diarrhea*** |  |  |
| Grade 1 | None | Consider Loperamide (4mg at first onset, followed by 2mg every 2 – 4 hours until diarrhea free for 12 hours)  Appropriate rehydration |
| Grade 2 | None | Loperamide (4mg at first onset, followed by 2mg every 2 – 4 hours until diarrhea free for 12 hours)  Appropriate rehydration |
| Grade 3 | Interrupt erlotinib | Loperamide (4mg at first onset, followed by 2mg every 2 – 4 hours until diarrhea free for 12 hours) **and** Interrupt erlotinib until resolution to Grade  1, and restart at reduced dose  Appropriate rehydration |
| Grade 4 | Discontinue Study | Loperamide (4mg at first onset, followed by 2mg every 2 – 4 hours until diarrhea free for 12 hours)  Appropriate rehydration |
| ***Rash*** |  |  |
| Grade 1 | None | Any of the following: minocycline a, topical tetracycline, topical clindamycin, topical silver sulfadiazine, diphenhydramine, oral prednisone (short course) at discretion of the investigator. |
| Grade 2 | None | Manage as described above |
| Grade 3  (or intolerable Grade 2) | Dose reduction; dose can be re-escalated when rash is  Grade 2 | Manage as described above |
| Grade 4 | Discontinue Study | Manage as described above |
| a Recommended dose: 200 mg po bid (loading dose) followed by 100mg po bid  7–10 days. | | |

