### Rash

Skin rash or dermatosis (Grade 1 – 2) has been observed during the first several days of treatment with erlotinib in more than 50% and has been observed to diminish in severity despite continued treatment in many patients. In some patients, particularly when a superimposed infection is suspected, this rash appeared to improve with topical and oral antibiotics. Anecdotal reports of improvement have occurred with several agents. In patients with severe rash, treatment may need to be discontinued or the dose reduced (see table 11 above).

See Appendix 5 for additional guidelines on the treatment of rash.

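### Section 12.5 orders both dose reduction and discontinuation for uncontrolled or untolerated Grade 4 diarrhoea or rash, and does not say which rule prevails

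*Protocol*

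**What the plan says.** The text of Section 12.5 (Dose Modifications for Toxicity) starts from a broad trigger: "In the event of toxicity (e.g., diarrhea, rash) that is not controlled by optimal supportive care", or that is "not tolerated due to any reason, regardless of severity, the daily dose of erlotinib will be decreased to 100 mg/day". A second step down to 50 mg is allowed. Discontinuation appears only as the last resort: "Patients who cannot tolerate this dose reduction will be permanently discontinued from the program".

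The text under Table 2 covers what follows a reduction. Toxicity must have improved by a set amount within two weeks, "or further dose reduction by one level will be required". It also permits, but does not require, a pause in dosing of up to two weeks.

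Table 3 sets actions by toxicity and grade for the same two toxicities. For Grade 4 diarrhoea and for Grade 4 rash, the dose-modification column reads "Discontinue Study". For Grade 3 diarrhoea it requires interruption, then a restart at a reduced dose. For Grade 1 and 2 diarrhoea and Grade 1 rash it lists no dose change.

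Elsewhere, the synopsis says "At any time during study, progression of disease, unacceptable toxicity or patient refusal will result in study treatment discontinuation", and Section 11.2 says "Patients will be treated until progression of disease or unacceptable toxicity". The rash paragraph of Section 12.7 says "In patients with severe rash, treatment may need to be discontinued or the dose reduced".

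**The concern.** The text names diarrhoea and rash as its own examples and states that grade does not matter. An uncontrolled or untolerated Grade 4 event of either kind therefore falls under both the text and Table 3. One rule keeps the patient on erlotinib at a lower dose; the other stops the drug. A site cannot obey both.

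What is at stake is mainly patient safety. Followed literally, the text continues the drug at the highest grade that Table 3 lists, for the two toxicities that Section 12.5 calls most common. There is a smaller reporting consequence. Section 12 names adverse events that lead to premature withdrawal as a safety item, so whether a given event carries that label could depend on which paragraph a site followed.

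**Working it through.** No figure in the protocol is in question, so the check is to apply each rule to the same patient. In every row below, the toxicity is assumed to be uncontrolled by supportive care or not tolerated, which is the text's trigger. The starting dose is 150 mg/day.

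| Situation | Text of Section 12.5 | Table 3 | Agree? |
| --- | --- | --- | --- |
| Grade 4 diarrhoea or rash at 150 mg | 100 mg/day (100/150 = 67% of the starting dose) | Stop | No |
| Grade 4 diarrhoea or rash after reduction to 100 mg | 50 mg/day (50/150 = 33%), under the further-reduction sentence | Stop | No |
| Grade 4 diarrhoea or rash at 50 mg | No lower level exists; stop if not tolerated | Stop | Yes |
| Grade 3 diarrhoea at 150 mg | 100 mg/day; a pause is optional | Interrupt, then restart at a reduced dose | In part |
| Grade 3 rash, or intolerable Grade 2 rash, at 150 mg | 100 mg/day | Dose reduction | Yes |
| Grade 1 or 2 diarrhoea, or Grade 1 rash, at 150 mg | 100 mg/day | No dose change | No |

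The first two rows are the safety-relevant conflict. The fourth and last rows show that the same literal reading produces other differences.

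The next step is to look for a sentence that decides between the rules. The candidates are:

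- **Section 12.5, opening sentence.** It tells sites to follow the organ system with the worst toxicity and points to Table 2. It does not rank the text against Table 3.
- **Section 12.5, text under Table 2.** It refers to Table 3 only for re-escalation after rash. On that topic it defers to the table, so re-escalation is not part of this point.
- **Section 11.2.** It refers to Section 12 as a whole for dose reductions, and it ends treatment for unacceptable toxicity without tying that to a grade.
- **Synopsis.** It makes discontinuation mandatory for unacceptable toxicity, again with no grade.
- **Section 12.6.** It takes patients off treatment when an interruption exceeds two weeks, which is a different situation.
- **Section 12.7, rash.** It names both actions for severe rash and assigns neither to a grade.
- **Sections 12.8 and 14.** They let investigators withdraw a patient, but this is discretion and does not rank the rules.

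None of these settles which rule applies at Grade 4.

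**The case against.** The strongest reply is that the two rules can be reconciled. The text is a general rule for any toxicity, and its any-severity wording most plausibly lowers the threshold: a patient may be reduced even when the grade alone would not call for it. Table 3 shows the same idea by treating intolerable Grade 2 rash like Grade 3. A site facing Grade 4 diarrhoea would look up the row that names it, and a specific row would ordinarily override a general sentence. This is a sensible reading and probably the intended one. But the protocol does not state it, and the words as written reach Grade 4 for the toxicities they name.

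The second reply is that safeguards exist. The synopsis and Section 11.2 end treatment for unacceptable toxicity, and Sections 12.8 and 14 allow withdrawal for adverse events or when continuing would harm the patient. This stands. A reader might infer that sites are bound to keep dosing a Grade 4 patient; the documents do not support that.

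The third reply is that little information would be lost. Section 12 requires reporting of erlotinib-related rash and of all serious adverse events, and a Grade 4 event would probably qualify as serious. This also stands: what may differ is the withdrawal label, while the event itself would normally be captured.

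A reader might also infer that the mismatch is confined to the Grade 4 rows. On the literal reading that creates the Grade 4 conflict, it is not: the low-grade rows and Grade 3 diarrhoea differ too.

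**Conclusion.** The point holds as a minor safety correction. For Grade 4 diarrhoea or rash that is uncontrolled or not tolerated, Section 12.5 orders continued treatment at 100 mg/day (or 50 mg/day after an earlier reduction) in its text and discontinuation in Table 3, with no order of precedence. The conclusion rests on reading the text as written and on taking the Table 3 entry as an order to stop the study drug, as its column heading indicates.

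The number of patients affected cannot be derived, because the protocol gives no Grade 4 rate. It is likely to be small: the Introduction describes these drugs as well tolerated with little severe toxicity, and Section 12.7 says diarrhoea seldom interfered with dosing. For the same reason, no percentage effect on the withdrawal rate can be stated.

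A reader might infer that the conflict weakens the three-month progression-free survival result. The documents do not support that. The conflict touches neither the endpoint definition nor the sample size derivation, and Sections 8 and 9.5 continue assessment to progression in patients who stop without it.

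**What to change.** In Section 12.5, add one clause both to the sentence ordering reduction to 100 mg/day and to the sentence under Table 2 requiring a further one-level reduction: *except where Table 3 requires discontinuation (Grade 4 diarrhoea or rash) or interruption (Grade 3 diarrhoea)*.

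Then add one sentence saying that the any-severity wording permits reduction for intolerable lower-grade toxicity even where Table 3 lists no dose change. This keeps the flexibility the text was probably meant to give and removes the low-grade mismatch as well.

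The cost is one clause used twice and one added sentence, made through the amendment procedure in Section 18.7. It needs no additional patients, visits or tests.

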**Table 2: erlotinib Dose Level Reductions**

| **Starting Dose** | **First Reduction** | **Second Reduction** |
| --- | --- | --- |
| 150mg | 100mg | 50mg |

Within 2 weeks following a dose reduction, erlotinib related toxicity must improve by at least one NCI-CTC grade and be NCI-CTC Grade  2 (Any ocular toxicity must improve to NCI-CTC Grade 1), or further dose reduction by one level will be required. Dosing may be interrupted for a maximum of 2 weeks if clinically indicated and if the toxicity is not controlled by optimal supportive medication.

Once a patient has had a dose reduction for toxicity, the dose will not be re-escalated except in the case of erlotinib related rash. In the event of a rash, dose can be re-escalated when rash is  Grade 2 (see table 3).

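### Section 12.5 both requires a further dose reduction and permits re-escalation for a rash that stays at Grade 2 after a reduction for intolerable Grade 2, and does not say which rule prevails

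*Protocol*

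**What the plan says.** Four places in the protocol bear on a patient whose dose has been lowered for rash.

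- **Section 12.5, opening text.** If a toxicity (rash is a named example) is uncontrolled or "not tolerated due to any reason, regardless of severity, the daily dose of erlotinib will be decreased to 100 mg/day". Then: "A second reduction to 50 mg is possible".
- **Section 12.5, text under Table 2.** "Within 2 weeks following a dose reduction, erlotinib related toxicity must improve by at least one NCI-CTC grade and be NCI-CTC Grade" 2 (a comparison sign before the 2 is lost), "or further dose reduction by one level will be required". The next paragraph bars re-escalation after a toxicity reduction except for erlotinib-related rash, where the "dose can be re-escalated when rash is" at a Grade 2 limit (sign again lost).
- **Section 12.5, Table 3, rash rows.** Grades 1 and 2 call for no dose change. The next row covers Grade 3 ("or intolerable Grade 2"): reduce, with re-escalation allowed at the same Grade 2 limit. This cell does not repeat the two-week improvement rule.
- **Section 11.2.** Directly after the 150 mg/day dose: "No dose escalation of erlotinib is permitted". The following sentence refers reductions for toxicity to section 12.

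**The concern.** The grade that can trigger a rash reduction (Grade 2, when intolerable) is also the grade at which the dose may be raised again. The improvement rule counts grades gained since the reduction. The re-escalation rule looks only at the current grade. A patient who starts at Grade 2 and stays there can fail the first test and pass the second.

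Section 12.5 names rash as one of the two most common adverse effects, and Table 3 is the grade-by-grade guide that a site is likely to consult. A site working from the Table 3 cell alone could raise the dose in a patient for whom the text under Table 2 requires it to be lowered. That is first a matter of patient safety. It also bears on toxicity and feasibility, both secondary endpoints in the synopsis, because in a multicentre trial sites could handle the same patient differently.

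**Working it through.** The protocol gives no figure to reproduce here, so the check is one of logic. Let B be the rash grade at reduction and N the grade two weeks later.

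- Further reduction is required unless B − N ≥ 1 and N is within the Grade 2 bound (text under Table 2).
- Re-escalation is permitted if N is within the Grade 2 limit (text under Table 2, and Table 3).

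With both lost signs read as at most Grade 2:

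| B | N | B − N | Further reduction required | Re-escalation permitted | Both |
|---|---|---|---|---|---|
| 2 | 2 | 0 | yes | yes | **yes** |
| 2 | 1 | 1 | no | yes | no |
| 2 | 0 | 2 | no | yes | no |
| 3 | 3 | 0 | yes | no | no |
| 3 | 2 | 1 | no | yes | no |
| 3 | 1 | 2 | no | yes | no |
| 3 | 0 | 3 | no | yes | no |

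Exactly one case meets both rules: reduced at Grade 2 and still at Grade 2. For a patient at the first reduced level of 100 mg, Table 2 makes the required step 50 mg, and the only level above is 150 mg.

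**Sensitivity to the lost signs**

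- Improvement bound: the sign does not matter for this case, because B − N = 0 already fails the one-grade test.
- Re-escalation limit read as printed, with no sign (exactly Grade 2): the case remains.
- Re-escalation limit read as strictly below Grade 2: the case disappears.
- Improvement bound strict and re-escalation limit at most 2: Grade 3 falling to Grade 2 would also meet both rules. This needs two different signs in adjacent sentences, and I do not rely on it.

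**Which sign is likelier.** Plain less-than and greater-than signs survive in the text (for example the laboratory limits in Section 7.1), while a gap stands where an inclusive sign would be natural (the life-expectancy criterion in the same section). That favours at most Grade 2. It is not proof: one inclusive sign survives in Section 11.2, and the Table 3 footnote has lost a symbol that need not be a comparison.

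**The opening text of Section 12.5.** It orders a reduction for intolerance at any grade, whereas Table 3 lists no dose change for Grade 1. A Grade 1 rash reduced on that basis and still at Grade 1 has B − N = 0, so further reduction is required, and it lies within the re-escalation limit on either the inclusive or the strict reading. The point does not rest on this case, but it shows why the opening text belongs in the reconciliation.

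**The case against.** **The two rules differ in force.** Further reduction is mandatory and re-escalation is optional, so an investigator who never uses the permission complies with both. The opening text of Section 12.5 also gives a rash that is still not tolerated a direction. This stands, and it makes the conflict milder than two opposite orders. It does not remove it: no precedence is stated, and the permission carries no tolerability condition that would exclude this patient.

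**The decisive character cannot be seen.** This also stands. The missing sign comes from reading the PDF and is not a fault of the plan. The point is conditional on the reading adopted.

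A reader might infer more, in four ways that the protocol does not support:

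- *Section 11.2 as a third, opposing instruction that holds the patient at 100 mg.* Its sentence follows the 150 mg/day dose and reads naturally as barring escalation above it. Section 12.5 treats re-escalation separately, as an explicit exception for rash. At most a cross-reference is missing.
- *Grade 3 improving to Grade 2 as a second conflict.* On the reading adopted, that patient has improved by one grade and owes no further reduction, and Table 3 asks for no dose change at a tolerated Grade 2.
- *Re-escalation at the very moment of reduction.* The Table 3 cell describes a sequence, reduction first and re-escalation afterwards.
- *A patient count.* Section 12.7 reports Grade 1–2 rash in more than 50%. The protocol does not say how many such rashes are intolerable, or how many of those stay at Grade 2 after a reduction. The section adds that rash lessens in many patients despite continued treatment.

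**Conclusion.** The point holds in a narrow form. On the likeliest reading, a patient reduced for intolerable Grade 2 rash and unchanged two weeks later meets both a mandatory further reduction and a permission to re-escalate, and the protocol does not rank the two. It is one case, in one toxicity, and it rests on the lost sign meaning at most Grade 2 (or exactly Grade 2). Confidence is therefore moderate.

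The number of patients affected is unknown. Nothing shows an effect on progression-free survival or on its decision rule, and differing practice between sites is a possibility, not something shown. The reason to act is consistent and safe handling of a common toxicity at very little cost. This is a needed clarification and not a flaw in the design.

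**What to change.** 1. The sponsor's clinicians should reconcile the opening text of Section 12.5, the text under Table 2 and the rash rows of Table 3. Either no patient should be able to meet the further-reduction and re-escalation conditions together, or the protocol should state which rule takes precedence.
2. The resulting rule should appear in identical wording in the text and in Table 3, so that a site using the table alone sees all of it.
3. As a clarification only, Section 11.2 should say whether its ban on escalation covers re-escalation after a reduction for rash.

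The dose, the threshold and the order of precedence are for the sponsor's clinicians; none is proposed here.

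The cost is a few sentences and one table cell, with no added patients or procedures. Because patient safety may be affected, Section 18.7 calls for a formal amendment with ethics committee approval before it is put into effect.

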**Table 3: Dosage Modification Criteria and Guidelines for Management of Study Drug Related Toxicities**

| **Toxicity,  NCI-CTC Grade** | **Study Drug Dosage Modification** | **Guideline for Management** |
| --- | --- | --- |
| ***Diarrhea*** |  |  |
| Grade 1 | None | Consider Loperamide (4mg at first onset, followed by 2mg every 2 – 4 hours until diarrhea free for 12 hours)  Appropriate rehydration |
| Grade 2 | None | Loperamide (4mg at first onset, followed by 2mg every 2 – 4 hours until diarrhea free for 12 hours)  Appropriate rehydration |
| Grade 3 | Interrupt erlotinib | Loperamide (4mg at first onset, followed by 2mg every 2 – 4 hours until diarrhea free for 12 hours) **and** Interrupt erlotinib until resolution to Grade  1, and restart at reduced dose  Appropriate rehydration |
| Grade 4 | Discontinue Study | Loperamide (4mg at first onset, followed by 2mg every 2 – 4 hours until diarrhea free for 12 hours)  Appropriate rehydration |
| ***Rash*** |  |  |
| Grade 1 | None | Any of the following: minocycline a, topical tetracycline, topical clindamycin, topical silver sulfadiazine, diphenhydramine, oral prednisone (short course) at discretion of the investigator. |
| Grade 2 | None | Manage as described above |
| Grade 3  (or intolerable Grade 2) | Dose reduction; dose can be re-escalated when rash is  Grade 2 | Manage as described above |
| Grade 4 | Discontinue Study | Manage as described above |
| a Recommended dose: 200 mg po bid (loading dose) followed by 100mg po bid  7–10 days. | | |

